#### Suspected unsuspected serious adverse reaction (SUSAR)

We do not anticipate any SUSARs in relation to this trial.

### Sample size

Given the lack of evidence related to the potential effect of probiotic use for the prevention of mastitis, we used the results from the comparable trials of antibiotics for the prevention of mastitis to determine effect sizes. Although the Cochrane review reported an overall 57% non-significant reduction in mastitis [24], with individual trials finding an up to 76% reduced risk [25], we chose a more conservative 50% reduction as a clinically meaningful treatment effect. Based on an expected rate of mastitis in the control group of 18% [9–11], two-sided 5% significance level and a power of 80%, we estimated a total sample size of 452 would be required. However, given studies related to the duration of breastfeeding report a cessation rate in the first 8 weeks post-partum of up to 20% [9, 15], and a potential loss-to follow-up of 5–10% may occur with withdrawals or non-compliance, we inflated the sample size by a further 30% to ensure complete data. Hence, we estimated a total sample size of approximately 600 women would be required (300 per group) for this trial, including all sites.

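### Multiplying 452 by 1.30 does not offset losses at the upper end of the plan's own 25–30% allowance: 600 women give about 80% power at 25% loss but about 77% at 30%

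*Protocol article*

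**What the plan says.** All of the inputs are in the Sample size section of the protocol article.

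- Control rate: "Based on an expected rate of mastitis in the control group of 18" per cent.
- Effect: "we chose a more conservative 50% reduction as a clinically meaningful treatment effect", which puts the probiotic arm at 9%.
- Error rates: "two-sided 5% significance level and a power of 80" per cent.
- Result before any allowance for loss: "we estimated a total sample size of 452 would be required".
- First allowance: "a cessation rate in the first 8 weeks post-partum of up to 20" per cent.
- Second allowance: "a potential loss-to follow-up of 5–10% may occur with withdrawals or non-compliance".
- Inflation step: "we inflated the sample size by a further 30% to ensure complete data".
- Final size: "we estimated a total sample size of approximately 600 women would be required (300 per group").

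The Statistical analyses section names an unadjusted chi-square test as the principal analysis. It calls for an intention-to-treat approach that takes in women lost to follow-up, non-compliant or withdrawn.

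**The concern.** The section presents the 30% increase as the answer to the losses it has just listed, with the aim of complete data. Added together, those losses run from 25% to 30%. A proportionate increase and a proportionate loss are different quantities: raising N by 30% offsets a loss of 1 − 1/1.30 = 23.1%, not 30%. If the inflation was meant to preserve 452 evaluable women over the whole allowance, it falls short at the upper end, and the 80% power given in the section is not delivered there. That figure matters most if the trial finds no difference, because readers will use it to judge what such a result rules out.

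**Working it through.** **Inputs** (Sample size section): p1 = 0.18; p2 = 0.18 × 0.50 = 0.09; two-sided α = 0.05 (z = 1.960); power 80% (z = 0.842); equal allocation; cessation up to 20%; further loss 5–10%; 600 randomised.

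**Step 1. Reproduce 452.** Use the two-proportion formula with pooled variance under the null and no continuity correction, which suits an uncorrected chi-square test:

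n per arm = [1.960 × √(2p̄(1 − p̄)) + 0.842 × √(p1(1 − p1) + p2(1 − p2))]² / (p1 − p2)²

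- p̄ = 0.135, so 2p̄(1 − p̄) = 0.23355 and the first term is 0.947.
- p1(1 − p1) + p2(1 − p2) = 0.1476 + 0.0819 = 0.2295, and the second term is 0.403.
- n = (0.947 + 0.403)² / 0.0081 = 225.1 (unrounded terms), so 226 per arm and **452** in total.

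This is the plan's figure exactly, and the starting point is sound.

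**Step 2. Identify the inflation.** 452 × 1.30 = 587.6, so 588, which is consistent with about 600. Dividing by 0.70 gives 645.7, so 646, which is not. Both the wording and the total point to multiplication.

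**Step 3. Set out the loss range.**

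- Added: 20% + 5% = 25% to 20% + 10% = 30%.
- Compounded: 1 − 0.80 × 0.95 = 24% to 1 − 0.80 × 0.90 = 28%.

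**Step 4. Size needed to keep 452, as 452/(1 − loss).**

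| Loss | Women to randomise |
|---|---|
| 24% | 595 |
| 25% | 603 |
| 28% | 628 |
| 30% | 646 |

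**Step 5. Power with 600 randomised.** With n evaluable per arm:

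power = Φ{[0.09 − 1.960 × √(0.23355/n)] / √(0.2295/n)}

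At 30% loss, n = 210. The numerator is 0.09 − 1.960 × 0.03335 = 0.02464 and the denominator is 0.03306, giving Φ(0.745) = 0.772.

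| Loss | Evaluable of 600 | Power, 18% v 9% |
|---|---|---|
| 24% | 456 | 80.5% |
| 25% | 450 | 80.0% |
| 28% | 432 | 78.3% |
| 30% | 420 | 77.2% |

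The unpooled version of the formula gives 77.7% at 420 evaluable, so the conclusion does not depend on that choice. At 30% loss the trial is 452 − 420 = 32 evaluable women short, equivalent to 646 − 600 = 46 fewer randomised than needed.

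**The case against.** Four points can be made for the plan.

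*No 30% loss is stated.* This is right. The only 30% in the section is the increase in N. A loss of 30% is the sum of two upper limits and assumes that no woman is counted in both. A reader might infer that the plan claims a 30% inflation covers a 30% loss, but the text makes no such claim. It does present the increase as its provision for losses that can add up to that figure, so testing the upper end is fair.

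*The lower end is covered.* Also right. A reader might infer that 600 fails throughout the range, because 452 is kept only up to a loss of 1 − 452/600 = 24.7%. But 452 includes a little slack from rounding 225.1 up to 226 per arm. At 25% loss the 450 remaining women still give 80.0%, and at the compounded lower end of 24% power is 80.5%.

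*Intention to treat may keep these women.* This is the strongest objection. The primary outcome is mastitis up to 8 weeks after birth, and its definition does not remove a woman when she stops breastfeeding. One who weans early but supplies outcome data can stay in the chi-square test. If only the 5–10% were missing, 540 to 570 women would remain, with power of 86.6% to 88.4% at 18% v 9%. That is a bound and not a forecast, since stopping breastfeeding could lower the event rates. It limits the practical weight of the point. It does not repair the stated step, because the sample size section counts cessation and non-compliance as losses.

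*The effect is small beside other uncertainty.* The Background section gives mastitis in 15–21% of breastfeeding mothers in Australia. With all 452 evaluable and a 50% reduction, power runs from 71.5% at 15% to 86.8% at 21%. A worst-case fall of about 3 points sits well inside that spread. This supports a low severity.

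**Conclusion.** The point stands as a minor error in the inflation step. The 452 is correct. Multiplying it by 1.30 and rounding to 600 secures about 80% power at the lower end of the plan's allowance (24–25% loss) but not at the upper end, where power is 78.3% if the losses compound to 28% and 77.2% if they add to 30%. The worst case is just under 3 percentage points below target.

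This rests on the plan's 18% v 9%, an uncorrected chi-square test, losses equal in the two arms, and women who stop breastfeeding or do not comply being counted as not evaluable, as the sample size section treats them. If the intention-to-treat analysis retains many of them, the shortfall shrinks or disappears. The documents therefore do not support saying that the trial will have 77% power, nor that 600 is too few across the whole range.

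**What to change.** Keep 600 and restate the end of the Sample size section along these lines: *600 women randomised give 80% power if no more than about 25% are not evaluable, and about 77% if 30% are not evaluable (420 women).* In the same place, say whether women who stop breastfeeding before 8 weeks count as lost to the primary analysis, in terms that agree with the intention-to-treat wording of the Statistical analyses section.

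The cost is a sentence or two. No extra women are needed, and neither the design nor the analysis changes. The only downside is a slightly less favourable power figure at the upper end of the loss range.

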### Statistical analyses

The analysis and reporting of the results will follow the CONSORT guidelines (http://www.consort-statement.org/). Primary and secondary outcomes will be analysed using an intention-to-treat approach, which includes all losses-to follow-up, non-compliances or withdrawals. Baseline characteristics will be compared between allocated treatment groups using frequencies and descriptive statistics. The principal analysis will use an unadjusted Chi-Square test to compare the incidence of mastitis between the two groups. The corresponding unadjusted relative risk with 95% confidence interval will also be calculated. Further analysis of the primary outcome will use multivariable logistic regression to examine the effect of adjusting for any imbalances at baseline or important predictors of mastitis (e.g. previous history of mastitis, antibiotic use, cracked nipples, or duration of breastfeeding). Additional unadjusted and adjusted analyses of all secondary outcomes will be performed using measures and multivariable models appropriate for the outcome. An analysis of women compliant with treatment (per protocol) will also be performed to assess the robustness of the primary findings. For all analyses, the number of cases with complete data and those with missing values will be reported. If necessary, reason for and type of missing data will be assessed to determine whether multiple imputation, sensitivity analysis or other approaches (“best” and “worst” case scenario, last value carried forward) will be required. Analyses will be performed using SPSS Version 24 (IBM SPSS Statistics, 2016 IBM Corporation, Chicago, IL) by an analyst not involved in any data collection and blinded to treatment allocation.

To assess the impact of the APP, the rate of primary and secondary study outcomes will be compared between the main study group and small sub-sample. Compliance rates in the ingestion of the intervention, and completeness and acceptability of data collected during daily and weekly follow-up will also be examined between the two study groups.

This protocol has been formatted according to the SPIRIT (Standard Protocol Items: Recommendations for Interventional Trials) guidelines (Additional file 1).

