## Background

Breastfeeding has been consistently shown to be protective against a broad range of immediate and long term infant and maternal health outcomes [1–3]. International guidelines recommend exclusive breastfeeding for all babies in the first 6 months of life as it provides the best nutritional start for infants and promotes their healthy growth and development. Given the positive benefits of breastfeeding, it is of concern that the 2010 Australian Institute of Health and Welfare (AIHW) National Health Survey reported less than 15% of women exclusively breastfeeding at 5 months of age, despite a 96% initiation rate at birth [4]. These findings suggest that more resources and research are required to identify and treat the underlying causes of breastfeeding cessation in order to extend the overall duration and improve long term maternal and child health outcomes.

Mastitis and the pain associated with the condition have been shown to be associated with the cessation of breastfeeding [5–7]. The World Health Organisation (WHO) defines mastitis as an inflammatory condition of the breast, which may or may not be accompanied by infection [8]. It occurs in 15–21% of breastfeeding mothers in Australia [9–11]. Most episodes occur in the first 6–8 weeks postpartum but can occur at any time during breastfeeding [12]. Almost one-third of women experience a recurrent episode [13–15], and up to 3% of women with mastitis develop a breast abscess, often necessitating hospitalisation [16, 17].

Little is known about the epidemiology and pathogenesis of this common condition [7]. Though not well described, the risk factors appear to be associated with milk stasis, nipple damage and maternal fatigue [8, 9]. Cracked nipples may facilitate entrance of microorganisms through the skin, and incomplete emptying of the breasts may result in milk stasis which provides a susceptible and receptive culture media for microorganisms. Decreased immunity and a lowered resistance to infection may be a result of maternal fatigue [8, 18–20]. Other risk factors include a history of mastitis with a previous child, using an antifungal nipple cream and using a manual breast pump [7, 21].

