### Randomisation

Randomisation to either “probiotic” or “placebo” will take place immediately after consent within 72 h of birth. The randomisation schedule will be prepared and centrally administered by a researcher not involved in patient care. A computer random number generator will be used to prepare the randomisation schedule in blocks of 4 and 6, and stratified by the incidence of previous mastitis. The randomisation sequence will be concealed until all data has been collected. The participant and researcher will be blinded as to treatment allocation. Participants using the mobile phone application system (APProve-Lite) will be randomised via a central password-protected web-based application developed by the APProve clinical trial unit. Concealment for participants using the ‘standard’ approach (not the APProve-Lite system) will be via opaque, sealed envelopes.

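### The principal test and relative risk ignore previous mastitis, the randomisation stratum: valid, but slightly conservative, with a confidence interval slightly too wide

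*Protocol article*

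**What the plan says.** The Randomisation section describes a computer-generated schedule "in blocks of 4 and 6, and stratified by the incidence of previous mastitis". No other stratification factor is named.

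The Background lists the same factor as prognostic: "Other risk factors include a history of mastitis with a previous child".

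The Statistical analyses section then sets the principal analysis: "The principal analysis will use an unadjusted Chi-Square test to compare the incidence of mastitis between the two groups". The effect estimate follows suit: "The corresponding unadjusted relative risk with 95% confidence interval will also be calculated".

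Adjustment comes second: "Further analysis of the primary outcome will use multivariable logistic regression to examine the effect of adjusting for any imbalances at baseline", or for "important predictors of mastitis (e.g. previous history of mastitis, antibiotic use, cracked nipples, or duration of breastfeeding". Previous mastitis therefore appears in an adjusted model, but as an example covariate in an analysis that is not the principal one.

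The Sample size section plans 18% mastitis in the control arm, a 50% reduction, a two-sided 5% level and 80% power. It arrives at 452 women, raised to about 600.

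**The concern.** Stratified blocks hold the arms nearly balanced on previous mastitis, so chance imbalance on that factor can hardly contribute to the difference between arms. The variance in an unadjusted chi-square test, and in the interval for the unadjusted relative risk, still includes that between-stratum variation. If the factor predicts mastitis, the reported standard error exceeds the true sampling variability. The interval is then wider than it need be and the test rejects a true null less often than 5%.

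Efficiency is at stake, along with agreement between design and analysis. The protocol explicitly fixes an unadjusted principal method, so this is not a detail left to a later analysis plan.

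**Working it through.** **1. The plan's own figure.** Two proportions, pooled variance under the null, no continuity correction; rates 0.18 and 0.09, mean 0.135:

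n per arm = [1.96 × √(2 × 0.135 × 0.865) + 0.8416 × √(0.18 × 0.82 + 0.09 × 0.91)]² / 0.09² = 225.1, rounded up to 226.

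The total is 452, exactly as stated, with 80.2% power. The trial was sized for the unadjusted test it names.

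**2. Assumptions.** The documents do not give the share of women with previous mastitis (q) or their relative risk of mastitis in the trial (r). I take q = 15-25% and r = 2-3 as the main range, and look outside it in step 5.

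**3. Excess in the standard error.** With overall rate p, the rate without previous mastitis is p₀ = p / [1 + q(r − 1)], and the difference between strata is d = p₀(r − 1). The share of outcome variance due to the stratum is R² = q(1 − q)d² / [p(1 − p)]. The reported standard error is too large by the factor 1/√(1 − R²).

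- At the planned effect (p = 0.135):
  - q = 0.15, r = 2: d = 0.135/1.15 = 0.1174; R² = 0.1275 × 0.1174² / 0.1168 = 0.015; factor 1.008.
  - q = 0.25, r = 3: d = 2 × 0.135/1.5 = 0.18; R² = 0.1875 × 0.18² / 0.1168 = 0.052; factor 1.027.
- Under the null (p = 0.18):
  - q = 0.15, r = 2: d = 0.18/1.15 = 0.1565; R² = 0.1275 × 0.1565² / 0.1476 = 0.021; factor 1.011.
  - q = 0.25, r = 3: d = 2 × 0.18/1.5 = 0.24; R² = 0.1875 × 0.24² / 0.1476 = 0.073; factor 1.039.

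**4. Type I error of the chi-square.** The effective critical value is 1.96 times the null factor:

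- 2[1 − Φ(1.96 × 1.0108)] = 0.048
- 2[1 − Φ(1.96 × 1.0387)] = 0.042

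**5. Power.** Simulation at 452 women: 200,000 runs per setting, stratified 1:1 allocation with an approximated incomplete last block, control rate held at 18%, treatment relative risk 0.5. CMH is the Cochran-Mantel-Haenszel test stratified by previous mastitis.

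| Prevalence | RR of previous mastitis | Chi-square power | CMH power | Chi-square type I error |
|---|---|---|---|---|
| 10% | 1.5 | 81.1% | 81.0% | 0.050 |
| 10% | 2 | 81.2% | 81.3% | 0.048 |
| 10% | 3 | 81.4% | 82.3% | 0.044 |
| 20% | 1.5 | 81.1% | 81.1% | 0.050 |
| 20% | 2 | 81.3% | 81.6% | 0.047 |
| 20% | 3 | 81.7% | 82.8% | 0.042 |
| 30% | 1.5 | 81.0% | 81.0% | 0.049 |
| 30% | 2 | 81.2% | 81.5% | 0.047 |
| 30% | 3 | 81.8% | 83.0% | 0.042 |

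The CMH test held 0.049-0.050 throughout. For 15-25% prevalence and r = 2-3, the gain runs from about 0.2 to just over 1 point at 452 women, and is about 0.2-0.8 points at 600. Even at r = 4, the gain at 452 is only about 2 points.

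**6. How much of the benefit the unadjusted test already collects.** Take q = 0.25, r = 3, 226 per arm, by normal approximation:

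- The chi-square threshold is 1.96 × √(2 × 0.1168/226) = 0.0630.
- The total variance term is 0.1476 + 0.0819 = 0.2295. The between-stratum part is 0.1875 × (0.24² + 0.12²) = 0.0135, which leaves 0.2160.
- Chi-square without stratified allocation: Φ[(0.09 − 0.0630)/√(0.2295/226)] = 80.2%.
- Chi-square with stratified allocation: Φ[(0.09 − 0.0630)/√(0.2160/226)] = 80.9%.
- Stratified test: the pooled stratum rates are 0.27 and 0.09, so the threshold is 1.96 × √[2 × (0.25 × 0.27 × 0.73 + 0.75 × 0.09 × 0.91)/226] = 0.0613, and power is 82.3%.

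So about a third of the gain, (80.9 − 80.2)/(82.3 − 80.2), comes from stratified allocation alone. The approximation puts the remaining gap slightly higher than the simulation does.

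**The case against.** The best defence is that nothing invalid is planned. The chi-square errs only on the conservative side, the sample size was computed for it, and a simple principal test is easy to report. All of that stands.

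A second defence is that adjustment is already planned, with previous mastitis the first example named. This stands in part, since the factor is not overlooked. But the model is not principal and its covariates are examples or depend on observed imbalance. It places the stratum beside antibiotic use, cracked nipples and duration of breastfeeding, which can arise after randomisation. The Outcome measures section lists all three among the secondary outcomes, although baseline versions of antibiotic use and earlier breastfeeding duration are also collected. Logistic regression also gives an odds ratio, whereas the chosen effect measure is a relative risk.

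A third defence is that the size rests on assumptions. That is right. First-time mothers are eligible and have no earlier lactation, so prevalence could be below 15%. At a relative risk of 1.5 there is no visible gain.

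A reader might infer two stronger points that the documents do not support:

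- **That the unadjusted analysis pushes power below plan.** It does not, as the 452 reproduces for exactly that test. Power falls to about 77-80% only if nearly all of the anticipated 25-30% (cessation plus loss) supplies no outcome, leaving 420-450 women. The plan states intention-to-treat, so women who stop breastfeeding need not leave the analysis. With only the 5-10% loss, 540-570 women give 87-88%.
- **That the benefit of stratifying is wholly thrown away.** The unadjusted estimate is itself less variable under stratified allocation. What falls short is the reported standard error.

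**Conclusion.** The point holds as a small matter of efficiency and coherence. The protocol balances on a factor it calls important and then sets a principal test and relative risk that leave it out.

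Under the assumed 15-25% prevalence and two- to threefold risk, the standard error is about 1-3% too large at the planned effect (up to 3.9% under the null). The test runs at roughly 0.042-0.048 in place of 0.05, and the power forgone at 452 women is at most a little over 1 point. The direction is certain if previous mastitis is prognostic. The size depends on two quantities that the documents do not give. The validity of the trial and its planned power are not in question.

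**What to change.** Make the principal analysis of mastitis to 8 weeks a Cochran-Mantel-Haenszel test stratified by previous mastitis as recorded at randomisation, with the Mantel-Haenszel relative risk and its 95% confidence interval. With a_k and c_k the probiotic and placebo cases in stratum k, n₁k and n₀k the arm sizes and N_k the stratum total:

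RR = Σ(a_k n₀k / N_k) / Σ(c_k n₁k / N_k)

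Keep the unadjusted chi-square test and relative risk as supportive analyses. Leave the further logistic model as exploratory, and do not rely on it to account for the stratum.

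The stratum is known for every woman at randomisation, so no new data, participants or procedures are needed. Because the published protocol names the principal test, the change should be recorded as a dated departure from that text, with its reason, before unblinding. If the sponsor prefers to keep the unadjusted test, the trial remains sound; the stratified result should then be pre-specified as the first supporting analysis.

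### The principal result is a relative risk but the adjusted model natively gives an odds ratio, with no conversion named, so a difference between them cannot be put down to adjustment alone

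*Protocol article*

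**What the plan says.** The Statistical analyses section of the protocol article sets out two results for mastitis up to 8 weeks.

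- The principal one: "The principal analysis will use an unadjusted Chi-Square test to compare the incidence of mastitis between the two groups". Its effect measure is named: "The corresponding unadjusted relative risk with 95% confidence interval will also be calculated".
- A second, adjusted one: "Further analysis of the primary outcome will use multivariable logistic regression to examine the effect of adjusting for any imbalances at baseline". The adjustment extends to predictors of mastitis, with these examples: "previous history of mastitis, antibiotic use, cracked nipples, or duration of breastfeeding".

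No effect measure is given for the logistic model. The article does not mention an odds ratio anywhere, and the only effect measure in its abbreviation list is the risk ratio. The planning effect in the Sample size section is also a reduction in risk: "we chose a more conservative 50% reduction as a clinically meaningful treatment effect".

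For secondary outcomes, the same section leaves both measure and model open. For the primary outcome it fixes the unadjusted measure and the adjusted model.

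**The concern.** The adjusted analysis is there to show what adjustment does to the primary result, so it will be read against the unadjusted relative risk. The treatment coefficient of a logistic model is a log odds ratio, conditional on the covariates. If it is reported in that form, two things other than correction of imbalance separate it from the relative risk.

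- **Scale.** With an outcome as common as 18% in controls, the odds ratio lies visibly further from 1 than the relative risk computed from the same women.
- **Non-collapsibility.** Adding a covariate that predicts mastitis moves the odds ratio away from 1 even when that covariate is perfectly balanced. This matters here because previous mastitis, the first example covariate, is also the stratification factor (Randomisation section) and so should be close to balanced by design.

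A reader who saw a stronger adjusted figure could credit it to correction of imbalance, and could not set it directly against the 50% planning target.

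**Working it through.** **Inputs**

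- Control risk: "Based on an expected rate of mastitis in the control group of 18"% (Sample size section).
- Effect: a 50% relative reduction (same section), so the probiotic risk is 0.18 × 0.50 = 0.09.
- Error rates: "two-sided 5% significance level and a power of 80"% (same section).
- Range for the control risk: 15–21% (Background section).
- 300 women per group (Sample size section).

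**Step 1: the plan's own figure.** The article says "we estimated a total sample size of 452 would be required". With the pooled-variance formula and no continuity correction, the mean risk is (0.18 + 0.09)/2 = 0.135 and

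n per group = [1.96 √(2 × 0.135 × 0.865) + 0.8416 √(0.18 × 0.82 + 0.09 × 0.91)]² / 0.09²
= (0.947 + 0.403)² / 0.0081 ≈ 225.1, rounded up to 226.

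The total is 452, an exact match. The design risks are therefore 18% and 9%.

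**Step 2: the same two risks on two scales, with no covariates.** OR = [p1/(1 − p1)] / [p0/(1 − p0)].

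| Control risk | RR | Probiotic risk | OR |
|---|---|---|---|
| 18% | 0.50 | 9% | (0.09/0.91)/(0.18/0.82) = 0.451 |
| 15% | 0.50 | 7.5% | (0.075/0.925)/(0.15/0.85) = 0.459 |
| 21% | 0.50 | 10.5% | (0.105/0.895)/(0.21/0.79) = 0.441 |
| 18% | 0.75 | 13.5% | (0.135/0.865)/(0.18/0.82) = 0.711 |
| 18% | 0.90 | 16.2% | (0.162/0.838)/(0.18/0.82) = 0.881 |
| 18% | 1.00 | 18% | 1.000 |

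At the design effect, a 50% reduction in risk is a 1 − 0.451 = 55% reduction in odds. The gap narrows with smaller effects and is nil at the null.

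**Step 3: a balanced predictor added.** The documents give neither the prevalence of previous mastitis nor its strength as a predictor, so these values are assumptions. Take a binary covariate with the same prevalence in both groups, and solve for the treatment odds ratio within strata that keeps the overall risks at 18% and 9%.

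Example with prevalence 20% and covariate odds ratio 3:

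- Control: 14.2% without the factor and 33.2% with it; 0.8 × 14.2 + 0.2 × 33.2 = 18.0%.
- Probiotic: 6.8% and 17.9%; 0.8 × 6.8 + 0.2 × 17.9 = 9.0%.
- Treatment odds ratio in each stratum: 0.44.
- Standardised relative risk: 9.0/18.0 = 0.50.

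Over prevalences of 10–30% and covariate odds ratios of 2–5, the conditional odds ratio runs from 0.45 to 0.42. The standardised relative risk stays at 0.50 throughout, because the covariate is balanced.

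**Step 4: sampling error for comparison.** At 300 per group, SE(log RR) = √[0.91/(300 × 0.09) + 0.82/(300 × 0.18)] = √(0.0337 + 0.0152) = 0.221. The expected 95% confidence interval around 0.50 is 0.50 × exp(±1.96 × 0.221), about 0.32 to 0.77.

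**The case against.** The strongest reply is that the article names a model, not a measure. That the adjusted result will appear as an odds ratio is an inference from the choice of logistic regression. A logistic model followed by standardisation to a relative risk complies with the text as written, and an analysis plan not shown here may specify it. The same model with treatment alone would also give an unadjusted odds ratio, so like could be set beside like. All of this stands. A reader might infer that the plan commits to an odds ratio, or that the two results cannot be compared at all; the article supports neither. What remains is that it fixes both the unadjusted measure and the adjusted model, and says nothing that puts them on one scale.

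The second reply is about size. The gap needs a non-null effect, 0.50 against 0.45 is small beside an interval of about 0.32 to 0.77, and the 55% figure misleads only someone who reads odds as risk. This stands too, and it sets the grade. It does not remove the point: both figures come from the same women, so the shift is systematic and a wide interval does not absorb it.

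The third reply is that a common scale would not by itself make the comparison clean. Antibiotic use, cracked nipples and breastfeeding duration are example covariates and also appear among the secondary outcomes (Outcome measures section). If measured after randomisation, they could move an adjusted relative risk as well. That is correct, and it limits the remedy to baseline covariates.

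**Conclusion.** The point holds as a minor matter of reporting and interpretation. The article gives the principal result as a relative risk and fits the adjusted one with a model whose native output is a conditional odds ratio, with no conversion named. If that output is reported as it stands and the effect is not null, the adjusted figure will look stronger from the change of scale alone: 0.45 against 0.50 at the design risks (0.46 to 0.44 over control risks of 15–21%), and 0.71 against 0.75 for a smaller effect. Non-collapsibility adds a further shift, to 0.42 at most under the covariate values assumed above. A difference between the two results then cannot be attributed to adjustment alone.

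It would be wrong to infer that the trial's main conclusion is at risk. The principal test, its relative risk and the sample size do not depend on the adjusted model, and the result to be read against the 50% target is already a relative risk. Logistic regression is itself a valid model for this outcome; the weakness lies only in setting its untransformed output beside a relative risk.

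**What to change.** State, before unblinding, that the adjusted primary result will be reported as a relative risk and a risk difference, each with a 95% confidence interval. They can be obtained by standardisation from the planned logistic model or by Poisson regression with robust standard errors. Limit the covariates in this analysis to those fixed at baseline, such as previous mastitis. If an adjusted odds ratio is also shown, put the unadjusted odds ratio beside it and note that the two can differ even without imbalance.

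The cost is a sentence or two of wording and a little extra analysis work; design, data collection and sample size do not change. A log-binomial model would also serve but may fail to converge, so robust Poisson regression or standardisation is the safer choice. The analyst should confirm that the chosen method is available in the named software, since the article does not say.
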